## Discussion

Only 33% of people with depression or anxiety receive any help from health services in England [5] and other developed countries in Europe and North America [3]. Public-facing websites, such as BWW, offering support and help may offer effective help delivered at scale to very large populations. Yet, the effectiveness of BWW has yet to be established, and our study will provide the first rigorous test of this.

The design of such a large automated study in one geographical area poses a number of methodological challenges, and our study design has a number of strengths as well as inevitable weaknesses.

### Strengths

The pragmatic design of the trial means that our estimates of effectiveness and cost-effectiveness are likely to be generalizable to other areas of the United Kingdom and other high income populations as this is a direct to the public study that does not rely on health service infrastructure that varies from place to place.

The public health (RE-AIM) approach of the REBOOT study will help to raise awareness of the possibility of digital intervention with a large group of people with depression and anxiety who are not currently engaged with primary care or mental health services. It will also explore whether it provides additional help to those who are already engaged with these services in relation to immediate moderated anonymized support and digital approaches to socialization and recovery that might be more convenient and approachable than comparable face-to-face approaches. It will provide a great deal of information surrounding the reach and adoption of such a resource and the role it plays in their well-being. We will know the clinical, sociodemographic, and health care service use of participants and visitors to the site who complete baseline information but decide not to be randomized as well as those who utilize the interventions, and completers and dropouts from the study. We will also be able to explore through process evaluation moderators and mediators of mental well-being through both treatment arms and in more detail in the BWW treatment arm by detailed quantitative and qualitative analysis of social messaging through BWW. Therefore, there is the opportunity through such process evaluation to improve the reach or effectiveness of digital interventions such as BWW and also to predict more clearly what the impact of BWW might be in an area outside Nottinghamshire if such services were commissioned [45]. The protocol is ambitious, but the feasibility of conducting a fully mobile randomized clinical trial for depression has been demonstrated recently with the randomization of 626 participants [46].

### Limitations

Therefore, we have carefully coproduced the REBOOT study website with e-mental website developers such as M-Habitat [47] and the lived experience of the Lived Experience Advisory Panel of service users, who have also contributed to the public health campaign, to reflect the experience of people of different ages, gender, and sociodemographic background with personal experience of depression and anxiety. By doing so, we hope that the REBOOT public health campaign and study website will engage and connect with people who have depression and anxiety in the community so that they will enter the study and continue in follow-up. We have also considered issues of intrinsic reward (eg, altruism, motivational statements, and feedback on completion) and extrinsic reward (reminders through text, email, and entry of completers into competitions) to encourage completion of data on the website at each time point [48]. Issues around access to the Internet, ownership of devices, and having access and competence with information technology may also be barriers to the use of the interventions that will be explored through qualitative interviews.

A further complication in the digital study is the issue of contamination. People with depression or anxiety might access BWW or Moodzone independently, although in the county of Nottinghamshire the opportunity to enroll in BWW is limited to access through the Armed Forces as new personal subscription has been suspended for the duration of recruitment and follow-up in the REBOOT study. Only one randomization is possible from each web browser within a 30 day period. Participants may be able to deceive the randomization process through access from a different computer or web browser or by clearing the cookie installed to prevent multiple attempts. Internet protocol (IP) address was not used as a marker to prevent multiple randomizations in case several people might be sharing the same computer. There may also be potential leakage with people who live outside Nottinghamshire using work postcodes that are within the county. Furthermore, there are potential problems with contamination through digital users utilizing alternative sources of digital support and information rather than the study treatment allocated to them. For instance people might join Facebook and offer support to each other even though it is not anonymized, and there is no profession moderation or support. If any of these occurred to a significant extent, it may be difficult to show real improvements in clinical and cost-effectiveness. To understand these potential sources of contamination, we are asking all participants about use of other sites.

The design of studies to evaluate the reach, adoption, clinical-effectiveness, and cost-effectiveness of direct to the public digital health interventions for mental health problems are important, given the reach, popularity, and low cost of such approaches in a world that is increasingly digitally connected even in the poorest countries of the world. However, we are in the early stages of understanding how to optimally design such studies.

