
Big White Wall (BWW) is a well-established digital service (website and apps) being accessed by approximately 13,000 people in the United Kingdom in the past year. Currently, BWW has been purchased by the armed forces, some universities, and 25% of clinical commissioning groups throughout England that provide free access to 98% of the users. Only 2% of the users are individuals who pay for the service through a £25 monthly subscription. It is also available or being piloted in the United States, Canada, Australia, and New Zealand.

BWW offers the following to people over the age of 16 years [14]: (1) Web-based assessment to assess common mental health problems and comorbid physical conditions; (2) moderated online peer support network: a community of peers, professionally staffed at all times, enabling safe, anonymous support through talking therapies and creative self-expression; (3) guided support: a range of self-managed and facilitated programs for individuals and groups for depression and anxiety and related issues such as sleep, smoking, and alcohol problems based on cognitive behavioral therapy (CBT) and social support principles; and (4) live therapy: a range of real-time therapies by instant text, audio, or video from a panel of approved BWW therapists offering CBT, interpersonal therapy, person-centered counseling, or integrative counseling.

On the basis of public health principles, BWW emphasizes a recovery model to improve well-being and is theoretically based on a social model of depression emphasizing autonomy, hopefulness, and support [14] (see [15] and [16] for reviews of the social model of depression). There are no waiting lists, eligibility criteria, or restricted opening hours (available 24/7). Specially trained counselors employed by BWW as *wall guides* facilitate interactions, ensuring that a culture of respect toward others, tolerance, mutual learning, and safety are maintained at all times. Mental well-being is seen as a systemic interplay of factors that contribute to an individual’s engagement with themselves, their social networks and communities, and the society in which they live. Mental well-being is also seen as being intimately connected with physical health and general well-being.

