Peer support Internet interventions take less effort for service users than Internet-guided CBT [18]. The involvement is usually ongoing and unrelated to psychiatric crisis, for example, suicide or self-harm, unlike crisis lines such as Samaritans. In principle, relief from depression or anxiety can be achieved through BWW by improving the quality and consistency of support [19]. The effectiveness of BWW may be in keeping with the social model of depression and anxiety on which it was conceived. The onset of depression and anxiety is precipitated by the self-perception of a potential or actual lasting and severe threat to the person's well-being from a life event or a life difficulty in the absence of social support (isolation) or insufficient social support [20]. Relief from depression or anxiety is achieved by improved quality and consistency of support or life events that offer fresh starts or increased security. People with personality dysfunction may obtain less relief from depression and anxiety but still benefit [21].

Thus, a person with depression and anxiety has access through BWW to appropriate psychosocial support when they require it. They are given guidance and are enabled to choose to intervene in their own mental well-being (empowerment). This early intervention approach may preempt the need for later intervention if the person becomes worse. Although guided, people are encouraged to make their own decisions on how to use BWW so they retain their autonomy because perceived control is thought to improve outcome in depression and anxiety [15,16].

Alternatively, the National Health Service (NHS) has developed a free website providing information on mental health conditions and locally available resources called NHS Moodzone. It does not provide anonymized moderated peer support.

The RE-AIM (model [22]), which is designed to enhance the quality, speed, and public health impact of translational research in a defined population, will be used as a framework for the study. Here it will be used to compare free access to BWW versus free access to information about depression and anxiety from the NHS Choices Moodzone website for people who score above depression or anxiety caseness in one area of England serving inner city, urban and rural areas, and where there is no current institutional or commissioned access to BWW.

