### Engagement Strategy

The public engagement strategy and recruitment to the study will run in parallel with each other. The engagement strategy will, for 1 month, publicize the study to NHS, local authority, and third sector organizations in Nottinghamshire a month before recruitment to the trial begins. The study will be integrated into the early intervention stream of the Clinical Commissioning Groups and Health and Well-being Board Mental Health Strategy for Nottinghamshire. A range of methods will be used to engage with potential study participants, including:

Identification of primary care practices and other groups of health professionals, for example, health visitors and community pharmacists that are known to have an interest in mental health and a willingness to adopt new interventions early after their introduction in one part of the county before moving to other partsIntroducing a local general media advertising campaign (eg, bus and tram adverts, newspapers, and radio), followed by a Facebook and social media campaignPresenting the study to interested community groups, targeting both the young (eg, further education colleges and universities) and old (eg, Age UK), vulnerable groups (eg, new parents living in disadvantaged areas, through Surestart), third sector mental health groups (eg, Mind branches in Nottinghamshire), and local organizations promoting self-help (eg, Self-Help Nottingham)Producing online and offline presentations and written materialsOther novel approaches as they might arise in public health and primary care, for example, public health message with receipts in high footfall supermarkets or shopping centers

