### Sample and Eligibility

Potential participants from the county of Nottinghamshire will be able to self-refer, and their eligibility will be assessed by an automated digital program on the study website. The study website requests GP practice contact details in case the participant is ineligible for the study.

The inclusion criteria are as follows:

Aged 16 years or overResident in the County of NottinghamshireScores between 10 and 20 on the 9-item Personal Health Questionnaire (PHQ-9) [25] and/or 10 or more on the 7-item Generalized Anxiety Disorder (GAD-7) questionnaire [26], indicating probable caseness for depression and anxiety, respectively, but not a definite diagnosis of depression or anxiety disorderAccess to the Internet through a computer, tablet, or smartphone (Windows, iPhone operating system [iOS, Apple Inc], and Android)Able and willing to give informed consent (through electronic consent)

The exclusion criteria are as follows:

Scores 21 or more on the 9-item Personal Health Questionnaire (PHQ-9, severe depression)Scores 2 or 3 on PHQ-9 item “thoughts that you would be better off dead or of hurting yourself in some way.”Scores below 10 on PHQ-9 and 7-item Generalized Anxiety Disorder (GAD-7) questionnaireBWW and Moodzone are only available in English. Therefore, the website will recommend to participants that if they do not feel that they are sufficiently proficient in the use of the English language, they need not take part. There will be no test of proficiency.

Participants who are ineligible for the trial because they score in the severe range on the PHQ-9 or signs of suicidality will be provided with an opportunity to request that the study team inform their GP, mental health care team, or carer of their current mood state. If they choose not to take this offer, the study team will follow this up on one occasion with an email to ask them again if they would like the team to inform their GP or care team. If they do not reply, the team will consider this confirmation that they do not wish us to act on their behalf.

Participants that are under age will be given details of local children’s mental health services. They will be informed that they may return to the study website if they turn 16 years within the recruitment period, should they still wish to participate.

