#### Randomization: Arm 2—Participants Allocated to Moodzone

Participants will be directed to the Moodzone area of the NHS Choices website, a free to access website providing information on mental health conditions and locally available resources. Participants will be able to access all of the available material on mental health, including depression and anxiety. The site contains reading material and suggestions about maintaining mental health and provides measures of depression and anxiety for visitors to use.

All participants will be asked about whether they have received or used any additional mental health resources during their time in the study. NHS Moodzone access is used as the control digital resource so that all the participants are offered some help for their problems with depression or anxiety, but the control group do not access moderated, anonymized peer social support.

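### Current Big White Wall users can be randomized: the eligibility screen does not ask about an existing account, and the article is inconsistent on whether such access exists in the county

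*Protocol article*

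**What the plan says.** The Background section of the protocol article describes the study area as one "where there is no current institutional or commissioned access to BWW". The same section states that "BWW has been purchased by the armed forces, some universities, and 25% of clinical commissioning groups throughout England", and that "Only 2% of the users are individuals who pay for the service through a £25 monthly subscription". The Limitations section then reports that, within the county, "the opportunity to enroll in BWW is limited to access through the Armed Forces as new personal subscription has been suspended" while recruitment and follow-up last.

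The section on Arm 2 explains the choice of comparator by saying that "the control group do not access moderated, anonymized peer social support". It adds that everyone will be asked about other mental health resources used while in the study. Limitations repeats that participants are asked about other sites, so that contamination can be understood.

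Sample and Eligibility lists the entry rules, which an automated program on the website applies. They cover age, county residence, PHQ-9 and GAD-7 scores, the PHQ-9 self-harm item, internet access and consent, with advice on English proficiency. No item concerns BWW. Randomization is unstratified.

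Sample Size and Justification states that the 6-week variance was inflated to allow for contamination. It plans on a 3-point difference with SD 12.0 in each arm.

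**The concern.** The trial compares an offer of free BWW access with signposting to an information site. A person who is already using BWW weakens that comparison wherever they are allocated. In the Moodzone arm they may go on using the experimental service. In the BWW arm they gain little that they did not have. Both move the estimated effect toward zero, and the risk is a missed or understated benefit, not a false positive.

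Suspending new personal subscriptions shows that the team wanted to close this route. The suspension does not reach people who already hold an account, and the eligibility check does not reach them either. Because that check is automated and self-referred, no member of staff would notice such a person at entry.

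The article also describes access in the county in two ways, so a reader cannot tell whether the planners regarded existing access as absent or as present and tolerated.

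**Working it through.** **Access statements side by side.** Background says the area has no institutional or commissioned access. Limitations says the Armed Forces route is open. Background itself names the armed forces as a purchaser of BWW, which makes that route institutional. As written, the two statements conflict. The Arm 2 sentence on the control group is unqualified, while Limitations accepts that people might reach BWW independently.

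**Do the existing safeguards keep current users out?**
- Suspension of subscriptions: new ones only.
- Questions about other resources and sites: described as covering time in the study, so they screen nobody out and do not define a group at baseline.
- Baseline service-use inventory: not said to ask about BWW.
- Variance inflation: changes the SD, not the difference.

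**The plan's own sample size.** Inputs from Sample Size and Justification: difference 3, SD 12.0, two-sided 5%, power 90%, zero pre-post correlation, 50% loss.
- Normal approximation: n per arm = 2 × [12 × (1.960 + 1.282) / 3]² = 336.2, so 337.
- The t-test version gives 338 (power 90.07%), which matches the plan.
- 676 / 0.5 = 1352, which also matches. There is no arithmetic error.

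**Sensitivity to existing users.** Let c be the share of analysed participants who already use BWW and gain nothing from allocation. The documents do not give c, so every value is an assumption. The expected difference is 3(1 − c). With 338 per arm, SE = SD × √(2/338), and power ≈ Φ(3(1 − c)/SE − 1.96).
- SD 12.0: SE = 0.923.
- Prior study's 6-week SDs of 8.1 and 9.18: pooled SD = √((8.1² + 9.18²)/2) = 8.66, SE = 0.666.

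| c (assumed) | Expected difference | Power, SD 12.0 | Power, SD 8.66 |
|---|---|---|---|
| 0% | 3.00 | 90.1% | 99.5% |
| 1% | 2.97 | 89.6% | 99.4% |
| 2% | 2.94 | 89.0% | 99.3% |
| 5% | 2.85 | 87.0% | 99.0% |
| 10% | 2.70 | 83.3% | 98.2% |

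**Which c is plausible?** Background gives about 13,000 UK users in the past year, 2% of them paying personally: 13,000 × 0.02 = 260 people nationwide. Of 1352 randomized, 5% is about 68 people and 10% about 135. The latter would be more than half of all UK personal subscribers, so the subscriber route alone cannot plausibly produce such shares in one county. The number of Armed Forces users in the county is not given.

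**The case against.** The strongest reply is that the plan has already dealt with this. It names independent BWW access as a limitation, suspends new subscriptions, asks about other sites and inflates the variance for contamination. Keeping SD 12 while also shrinking the difference therefore counts contamination twice. At the prior study's SD, power would not fall to 90% until c reached about 28% (3.2415 × 0.666 = 2.16; 1 − 2.16/3 = 0.28). Assuming zero pre-post correlation is a further margin in a covariance-adjusted analysis. This largely stands as an argument about power. It does not stand as an argument about the estimate: a larger SD does not restore a diluted mean difference, and nothing listed prevents the dilution.

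The formula 3(1 − c) is also a worst case. Access is not use, and someone entitled to BWW who never enrolled would still be changed by the offer. This stands, and it is why the point concerns current account holders only.

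A charitable reading can soften the inconsistencies. Background may mean local commissioners and institutions, and the Arm 2 sentence may describe what is offered and not what people do. If so, a few words would make that clear.

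A reader might infer further routes. Limitations mentions "people who live outside Nottinghamshire using work postcodes that are within the county", some universities buy BWW, and recruitment is aimed at universities among others. The documents do not say that any such entrant holds BWW access or that any Nottinghamshire university has bought it, so these routes remain conjecture.

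**Conclusion.** The gap is real and probably small. The entry rules do not ask about a current BWW account, the suspension covers only new personal subscriptions, and the Armed Forces route stays open. Current users can therefore enter either arm and dilute the effect toward zero. The description of access in Background also conflicts with that in Limitations.

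A reader might go on to infer that the trial is materially underpowered. The documents do not support that. They give no prevalence of existing use, the stated sample size reproduces, and the power figures are sensitivity values that rest on an assumed c, on no benefit of allocation for existing users, and on the true SD being as high as 12. Under those conditions power is about 89% at c = 2% and 87% at c = 5%; with an SD near 8.66 it is about 99% in both cases. This is a cheap improvement to the design, not a flaw that threatens the trial.

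**What to change.** Add one item to the automated eligibility screen asking whether the person currently has a BWW account, and a matching exclusion criterion in Sample and Eligibility. If exclusion is not wanted, or recruitment is too far advanced, record the answer at baseline and prespecify a sensitivity analysis of the primary outcome without those participants.

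Do not extend the exclusion to past users or to people who merely have an entitlement through an institution. That would remove people for whom the offer is still new, in a pragmatic trial that sets out to study reach and representativeness.

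Reconcile the Background statement on institutional access, and the Arm 2 statement on what the control group accesses, with the Armed Forces route and the contamination described in Limitations.

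The cost is one website question and a short amendment. A few applicants would become ineligible, and the item depends on honest self-report.

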**Results:**

The primary outcome will be the Warwick-Edinburgh Mental Well-Being Scale at 6 weeks. We will also explore the reach, maintenance, cost-effectiveness, and barriers and drivers to implementation and possible mechanisms of actions using a range of qualitative and quantitative methods.

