Patient and public involvement is central to the design and delivery of this study. A user consultant has been appointed to develop novel approaches and monitor, iterate, and evaluate the effectiveness of the different engagement methods, with an action-research type approach. The user consultant will develop a lived experience advisory panel to help shape the study process throughout. They will work with at least one GP knowledge broker (who will act as clinical champions for the study as a whole) in other areas where BWW has been implemented successfully; this role has been important linking with GP and other community health professionals and the early intervention stream. Regular checks will show which methods are best for broadening the reach of the study and BWW to a wider range of people and groups and especially those isolated.

On the basis of 6- to 12-month engagement strategies using a part-time engagement officer carried out by BWW in the West Midlands (Dudley, Wolverhampton, and Walsall; in total a similar size population to that of Nottinghamshire), 1950 participants (1.6% of the population) were recruited. We anticipate a similar rate of recruitment in Nottinghamshire, with approximately 2200 participants recruited to our study website over a 12-month recruitment period, and we will have the additional help of the user consultant and the public health campaign publicizing the study.

The learning achieved from the recruitment period will inform the best approaches to engage with the public in later stages of the study. A feedback conference will engage with study participants and other stakeholders groups (commissioners, Improving Access to Psychotherapy services, public health, etc) to enable understanding of the wider validity and relevance of emerging findings. An effective public dissemination strategy, informed by our earlier learning, will communicate the findings of the research to a wide audience to help mobilize the new knowledge as part of the implementation strategy (see later section).

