Information for participants and the associated consent forms are provided electronically within the study website. Participants who wished to discuss the study could email and telephone the study team if they had any further questions before consenting to the study. An email confirming consent is sent to a participant once they have fully enrolled in the study.

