### Expected Duration of Participant Participation

Participation in the study will be for 6 months (see Figure 1 for participant journey through the study). Participants will receive electronic follow-up invitations at 3, 6, 12, and 26 weeks after randomization to be completed on the website. Participants may also be asked to take part in a short interview by phone or face-to-face to talk about their experiences of services and/or the study no later than 3 months from the ending of their participation.

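### The only duplicate control described, a 30-day browser lock, lapses before the 6-week primary endpoint, so a Moodzone participant can be randomised again without breaking any stated rule

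*Protocol article*

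**What the plan says.** The Limitations section gives the rule: "Only one randomization is possible from each web browser within a 30 day period". The rule is enforced by a cookie, and the authors accept that someone could defeat it "from a different computer or web browser or by clearing the cookie installed to prevent multiple attempts". They add that "Internet protocol (IP) address was not used as a marker to prevent multiple randomizations", because several people may share a computer. The same section says that "new personal subscription has been suspended for the duration of recruitment and follow-up in the REBOOT study", which leaves the Armed Forces as the remaining way into BWW in the county. The stated response to contamination is to ask all participants about their use of other sites.

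The time frames appear elsewhere. The abstract says: "The primary outcome will be the Warwick-Edinburgh Mental Well-Being Scale at 6 weeks". The section on expected duration says: "Participants will receive electronic follow-up invitations at 3, 6, 12, and 26 weeks after randomization to be completed on the website". The Engagement Strategy section expects "approximately 2200 participants recruited to our study website over a 12-month recruitment period".

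The inclusion and exclusion criteria under Sample and Eligibility do not mention earlier enrolment or randomisation. That section also says: "An email confirming consent is sent to a participant once they have fully enrolled in the study". The website therefore holds an email address for each enrolled person.

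**The concern.** A lock against repeat randomisation should last at least as long as the period in which a repeat entry can do harm. This one is shorter than the time to the primary endpoint, the follow-up and the recruitment period. Once it lapses, a person who was allocated Moodzone, still meets the symptom thresholds and finds recruitment open can enter again from the same browser. Nothing in the article forbids it. The suspension of personal subscription gives a reason to try, because a new randomisation is then almost the only way to obtain BWW.

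Two things are at stake. First, one person may supply records to both arms. Those records are dependent, yet the sample size section says that no clustering operates apart from repeated measures. Second, controls who obtain BWW pull the Moodzone mean towards the BWW mean, which dilutes the intention-to-treat contrast. Asking about use of other sites may reveal some exposure, but it does not show that two trial identities belong to one person.

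**Working it through.** **Inputs.** From Sample Size and Justification: difference 3 points, SD 12.0 per arm at 6 weeks, two-sided 5% level, 90% power, zero pre-post correlation, 338 per group, 50% loss. From the other sections cited above: 30-day lock, 6-week endpoint, 26-week follow-up. The 1:1 ratio is implied by 338 per group. The article gives no retry rate, so 10% to 20% is an assumption.

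**1. Reproduce the plan's figure.** With zero correlation, analysis of covariance reduces to a two-sample comparison:
n per arm = 2 × (1.960 + 1.282)² × 12² / 3² = 336.2, rounded up to 337 (674 in total). The plan gives 338 and 676, so it is reproduced within rounding. 676 / 0.5 = 1352, as stated. Power at 338 per arm is 90.1%.

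**2. Lock against time frames.**
- Primary endpoint: 6 × 7 = 42 days, and 42 − 30 = 12 days unprotected.
- Follow-up: 26 × 7 = 182 days, and 30 / 182 = 16% covered.
- Further entries from one browser with no circumvention: one before week 6 (day 30), and up to six before week 26 (days 30 to 180) if recruitment is still open.

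**3. Chance of reaching BWW.** After k further randomisations it is 1 − 0.5^k: 50% for k = 1 and 98.4% for k = 6.

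**4. Dilution at week 6.** Let f be the share of controls who retry once at day 30. The share who gain BWW is c = 0.5 f, and the diluted difference is 3 × (1 − c). The standard error is 12 × √(2/338) = 0.923, and power = Φ(difference / 0.923 − 1.960).

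| f | c | Difference | Power |
|---|---|---|---|
| 0 | 0 | 3.00 | 90% |
| 10% | 5% | 2.85 | 87% |
| 20% | 10% | 2.70 | 83% |

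**5. Duplicate records.** With 1352 randomised, 676 are controls. 676 × 0.10 = 68 and 676 × 0.20 = 135 extra records. As shares of all rows these are 68 / 1420 = 4.8% and 135 / 1487 = 9.1%.

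**6. The plan's contamination allowance.** 12.0² / 9.83² = 144 / 96.6 = 1.49, the inflation of almost 50% that the plan describes. Without it, the standard error is 9.83 × √(2/338) = 0.756. Power at 2.85 is then Φ(2.85 / 0.756 − 1.960) = 96%, and at 2.70 it is Φ(2.70 / 0.756 − 1.960) = 95%.

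**The case against.** The strongest reply has four parts.

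*The authors already disclose the problem.* They do disclose deception of the lock by another device, another browser or a cleared cookie, and they warn that contamination may hide real improvement. They do not say that the rule itself permits re-entry after 30 days, so this defence covers only part of the point.

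*The article is condensed.* Email uniqueness or a duplicate-cleaning rule may stand in the full protocol, the website specification or the analysis plan. This is fair: the lock can be called the only control that the article describes, not the only one that exists. But the 30-day limit is a stated rule and is too short as stated. The authors' remark that clearing the cookie may be enough also suggests that no identity check lies behind it.

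*The effect on power is small.* This largely stands. A day-30 entrant has at most 12 days of BWW before week 6, the 3-week measurement is untouched, and a retrier must consent, qualify and complete the baseline questionnaires again. Step 6 shows that the margin bought by the inflated SD covers the assumed dilution. That margin does not correct a diluted mean difference or dependence between one person's records.

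*Stronger conclusions are tempting but not supported.* A reader might let controls retry three times, so that 1 − 0.5³ = 87.5% of retriers reach BWW and, at the same 10% to 20% retry rate, power falls to about 84% to 76%. Expiry allows only one retry before week 6; more would need the circumvention already disclosed. A reader might also infer that motivated re-entrants fill the BWW arm. Each re-entry is itself randomised 1:1, so repeat entries fall on both arms equally in expectation.

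**Conclusion.** The point holds as a flaw in a stated design rule. The 30-day lock ends before the primary endpoint and long before the end of follow-up and recruitment, and no eligibility criterion closes the gap.

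The size cannot be determined from the article. If 10% to 20% of controls retry once at day 30, 5% to 10% obtain BWW before week 6 and power falls from 90% to about 87% to 83%. For that retry rate this is an upper bound on the loss, because it credits late entrants with the full 3-point effect and uses an SD that already allows for contamination. The 12- and 26-week outcomes are more exposed, since further entries become possible without circumvention while recruitment is open. The sample size is not in error on this point. The more lasting problem is one person counted in both arms, which a larger sample does not cure.

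**What to change.** 1. Make the email address a unique key for the whole recruitment and follow-up period, in addition to or in place of the 30-day cookie. Unlike an IP check, this does not block different people who share a computer.
2. Add prior randomisation in this trial to the exclusion criteria.
3. Before unblinding, and before identifiers are removed from the downloaded data, flag probable duplicates on whatever is held: email, and postcode, age and gender where recorded. The article makes collection of those last items conditional on not deterring participation, so matching may be incomplete.
4. State that only each person's first randomisation enters the primary analysis, in the arm first allocated, and report the number of later entries removed. This removes dependence between records. It does not undo dilution among controls who have already obtained BWW, so blocking re-entry matters as well.

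If recruitment is under way, steps 3 and 4 can still be adopted, since the article says the analysis plan will be finalised before database lock.

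The cost is a small website change and one data-cleaning rule. People who share an email address would need a second one, and a determined repeater could still use another address; step 3 is there to catch some of these.
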